### Secondary analyses

For the dose response relationship between change in HOOS ADL, the analysis will be similar to the analysis for change in gait speed outlined above.

The relationship between exercise compliance and HOOS subscales (symptoms, pain, quality of life), 30-s chair stand test and hip muscle strength will be presented as means with CIs or medians with IQRs within each of the compliance quartiles, as well as graphical representation of these values.

### Exploratory analyses

To better understand what may relate to how patients comply with prescribed rehabilitation exercise after THA, we will investigate how different variables relate to exercise compliance (dependent variables: time under tension summary dose and total number of exercise sessions), using uni-variable modelling. Independent variables will be: pain flares (first two weeks of intervention), pain flares (entire intervention period), HOOS pain (baseline), motivation to perform exercises, belief in effect of exercises, self-belief in compliance to exercising, satisfaction with rehabilitation exercise, physical activity (mean upright time/day and mean number of steps/day) and self-efficacy (baseline).

To better understand what may relate to how physically active patients are after a THA, we will investigate how different variables relate to physical activity (dependent variables: mean upright time/day and mean number of steps/day), using univariate modelling. Independent variables will be: pain flares (first two weeks of intervention), HOOS pain (baseline), motivation to perform exercises, self-belief in compliance to exercising, and self-efficacy (baseline).

In the analysis of "result of the operation", the change in score from baseline to follow-up will be presented for each HOOS subscale (pain, symptoms, ADL, QOL) and gait speed. Data will be presented both for each response category of the anchor question, and for the subgroup of patients, who answered "excellent", "very good" or "good" data. This subgroup is considered to be reporting a hip-specific acceptable symptom state. Data will be presented by means with 95% CI or medians and interquartile ranges (IQR). In each response category of the question for "change in hip problems", the change in score from baseline to follow-up will be presented for each HOOS subscale (pain, symptoms, ADL, QOL) and gait speed. Data will be presented by mean scores with 95% CI or median and inter quartile range (IQR).

Furthermore, for each exercise dose quartile, the percentage of patients in each response category of the questions for "result of the operation" and "change in hip problems", will be presented graphically. Finally, HOOS cut points for PASS and MCII will be estimated by the mean score or mean change approach
^40^.

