### Other pre-specified outcomes

Self-efficacy.The general self-efficacy scale
^30^ will be used to measure self-efficacy, defined as an individual's belief in his or her capacity to execute behaviors necessary to produce specific performance attainments. At 3 weeks after surgery.24-hour physical activity (mean upright time/day and mean number of steps/day).An ActivPAL movement-sensor will be used to measure mean time per day in upright position (standing and walking) based on 7 days of data collection. The sensor will be applied 3 weeks after surgery and used the following week. At 4 weeks after surgery.Number of participants with adverse events.Number and type of adverse events will be registered by the physiotherapist 3 and 10 weeks after surgery in the following pre-defined categories: Hip dislocation, infection, fracture, wound seepage, acute myocardial infarction, deep venous thrombosis, readmission and other.Mean change in pain after each exercise session.The visual analogue scale (VAS) will be used to assess pain before and after each exercise session. Data will be summarized as a mean change in pain per exercise session for the entire intervention period. At 10 weeks after surgery.Number of pain flares after exercise sessions.VAS will be used to assess pain before and after each exercise session. Pain flare is defined as an increase in pain of ≥20 mm
^31^. Data will be summarized, both for the first 14 days of the intervention and for the entire intervention period. At 5 and 10 weeks after surgery.Motivation to perform the prescribed exercises.The participants will be asked about their motivation to perform the prescribed exercises. A short questionnaire comprising three questions developed for this purpose will be used (the questionnaire is available as
*Extended data*)
^20^. The possible responses are ordered in 4 levels of motivation on an ordinal scale. At 3 weeks after surgery.Evaluation of the prescribed exercisesThe participants will be asked to evaluate the exercises. A short questionnaire comprising three questions developed for this purpose will be used (the questionnaire is available as
*Extended data*)
^20^. The possible responses are ordered in 4 levels on an ordinal scale. At 10 weeks after surgery.

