Change in hip problems	Descriptive statistics, no hypothesis	Patient reported rating of percieved problems in the operated hip now compared to before surgery (ordinal scale)	In each response category, the change in score from baseline to follow-up will be presented for each HOOS subscale (pain, symptoms, ADL, QOL) and gait speed. Data will be presented by mean with 95 % confidence intervals (CI) or median and inter quartile range (IQR). Furthermore, HOOS cut points for MCII will be estimated.
4. Other pre-specified outcomes			
Pain after exercise sessions	Descriptive statistics, no hypothesis	Change in pain per exercise session (score, continuous) Pain flare (increase in pain of ≥20 mm) during the first 14 days of the intervention (number, continuous) Pain flare for the entire intervention (number, continuous)	Summary statistics
Motivation to perform prescribed exercises	Descriptive statistics, no hypothesis	Motivation to perform exercises (ordinal scale) Belief in effect of exercises Self-belief in compliance to exercise	Summary statistics
Evaluation of prescribed exercises	Descriptive statistics, no hypothesis	Satisfaction with rehabilitation exercises Compliance with bandCizer Study-related change of exercise adherence	Summary statistics
Adverse events	Descriptive statistics, no hypothesis	Hip dislocation, infection, fracture, wound seepage, acute myocardial infarction, deep venous thrombosis, readmission, other)	Summary statistics

Descriptive analyses will be performed for demographic variables, supplementary descriptive variables, adverse events, motivation to perform prescribed exercises, evaluation of prescribed exercises and pain after exercise sessions (change in pain and pain flares). Data will be presented as means with 95% confidence intervals (CI) or medians with inter quartile ranges (IQR) for continues variables and as frequencies with percentages for categorical variables.

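### Counting pain flares, rather than flares per session, biases their exploratory association with exercise dose in the positive direction

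*Protocol article*

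**What the plan says.** Under Other pre-specified outcomes, the article ties pain ratings to training: "VAS) will be used to assess pain before and after each exercise session". It then sets the threshold: "Pain flare is defined as an increase in pain of ≥20 mm". The outcome is titled "Number of pain flares after exercise sessions", and Table 3 gives its scale as "Pain flare for the entire intervention (number, continuous"), with a matching entry for the first 14 days.

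Under Exploratory analyses, compliance is the outcome ("dependent variables: time under tension summary dose and total number of exercise sessions), using uni-variable modelling"), and the list of predictors begins: "Independent variables will be: pain flares (first two weeks of intervention), pain flares (entire intervention period), HOOS pain (baseline), motivation to perform exercises". Table 3 repeats this, lists dose both per week and in total, and labels the row as an exploratory look at association without a hypothesis. Neither place divides flares by the number of sessions performed.

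Flares in the first two weeks are also a predictor of physical activity. Of the ActivPAL the article says: "The sensor will be applied 3 weeks after surgery and used the following week".

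**The concern.** No session means no flare. A participant's expected flare count is the number of sessions performed multiplied by that person's flare risk per session. Regressing sessions on that count puts the outcome inside the predictor. The whole-period count covers exactly the sessions being explained. The 14-day count covers the first part of them, and that part also belongs to total dose. TUT accumulates over the same sessions, so the bias there has the same direction.

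The analysis is meant to help understand what relates to compliance, and the Discussion expects the study's results to be useful for practice and for planning a randomised trial. A positive coefficient could be read as flares going along with more exercise, even if patients prone to flares in fact train less.

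**Working it through.** **Inputs from the protocol.** n = 88 (Sample size). Training every second day for 7 weeks (Intervention) gives 49/2, or about 25 sessions, of which 14/2 = 7 fall in the first 14 days and 18 later. The protocol states no figure for this analysis. The 88 comes from the primary slope; it reproduces (power 0.9026 at 88, 0.8993 at 87) and is not in question.

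**Assumptions (not in the protocol).** Adherence a varies between patients as Beta(12,2) (narrow, mean 86%), Beta(16,4) (mean 80%) or Beta(4,2) (wide, mean 67%). Flare risk per session p has mean 5% to 20% and follows a Beta distribution with concentration 5 (patients differ widely) or 20 (patients are more alike). There is no true effect: p is independent of a.

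**Formula.** Let S be sessions and F the whole-period flare count.
- Cov(F,S) = E(p)·Var(S), so corr(F,S) = E(p)·SD(S)/SD(F), which is positive whenever S varies.
- Var(S) = 25·E[a(1−a)] + 625·Var(a).
- Var(F) = E(S)·E[p(1−p)] + E(S²)·E(p²) − [E(S)·E(p)]².

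**Low corner:** Beta(12,2), mean risk 0.05, concentration 5.
- E(S) = 21.43; Var(S) = 2.86 + 5.10 = 7.96; SD 2.82.
- Var(p) = 0.0475/6 = 0.0079; E(p²) = 0.0104; E[p(1−p)] = 0.0396.
- Var(F) = 0.85 + 4.87 − 1.15 = 4.57; SD 2.14.
- r = 0.05 × 2.82/2.14 = **+0.07** (simulated mean about +0.06).

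**High corner:** Beta(4,2), mean risk 0.20, concentration 20.
- E(S) = 16.67; Var(S) = 4.76 + 19.84 = 24.60; SD 4.96.
- Var(p) = 0.16/21 = 0.0076; E(p²) = 0.0476; E[p(1−p)] = 0.1524.
- Var(F) = 2.54 + 14.40 − 11.11 = 5.83; SD 2.41.
- r = 0.20 × 4.96/2.41 = **+0.41**.

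With n = 88, the two-sided 5% limit is |r| = 1.988/√(86 + 1.988²) = 0.21, so the two corners fall well below and well above it.

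**Simulated false significance, no true effect**

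| Predictor and outcome | Setting | Falsely significant |
|---|---|---|
| Whole-period count, sessions | full range above | about 5% to 99% |
| Whole-period count, sessions | Beta(16,4), conc. 5, risk 5/10/20% | 8/13/30% |
| Whole-period count, sessions | Beta(4,2), conc. 5, risk 10/15/20% | 46/69/85% |
| 14-day count, sessions | Beta(16,4), conc. 5, risk 5/10/20% | 6/11/23% |
| 14-day count, sessions | Beta(4,2), conc. 5, risk 10/15/20% | 31/47/63% |
| Whole-period count, TUT | conc. 5; conc. 20 | 5% to 48%; up to 76% |
| Flare proportion, including days 1–14 against later sessions | full range | 4% to 9% |

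The TUT results need one more assumption, the variation in TUT per session (log-SD 0.3 where it was stated).

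**If pain does deter training.** A second simulation used mean adherence of about 75–80%, spread of 1.0 or 1.5 on the logit scale, and mean flare risk 5% to 30%. The true correlation between flare risk and sessions was about −0.11 to −0.36. The whole-period count gave a mean r between −0.09 and +0.52. It was positive in 21 of 24 settings and near zero or weakly negative in the other three (−0.002, −0.04, −0.09). The per-session proportion was negative in all 24 (−0.05 to −0.30). For example, at risk 0.20, concentration 20, spread 1.0 and true r = −0.34, the count gave +0.21 (significantly positive in 51% of runs) and the proportion −0.23.

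**The case against.** - **Size.** The protocol supplies neither flare frequency nor spread of adherence. With rare flares, large differences in risk between patients and fairly uniform adherence, false significance is close to nominal. This stands. A reader might infer that a false positive is likely, or that a deterrent effect will be reversed; the documents support neither, because both depend on unstated quantities. The direction of the bias does not.
- **Purpose.** A reader might take this as the analysis that identifies barriers to exercise. The protocol claims less: an exploratory association without a hypothesis, in two of about ten predictors. Refining the intervention is assigned mainly to the qualitative study. This limits the consequence. It does not make a coefficient with a built-in positive component informative.
- **Definition.** The scale in Table 3 stands in a row analysed by summary statistics, while the regression rows say only pain flares, so an analysis plan could rescale the variable. That is possible, but the outcome's title and its only stated scale are both a number, and no other version is mentioned.
- **Physical activity.** A reader might extend the same fault to these models. Their outcome is upright time or steps, not sessions, so the shared-session mechanism does not apply directly. What remains is a mismatch of time windows.
- **Remedy.** A proportion from at most about 7 early sessions is coarse, and participants with no early session, who are clear non-compliers, drop out. Both are real costs.

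**Conclusion.** The concern holds for direction. As defined, the flare count is tied to the sessions that make up the outcome, so its association with dose is biased in the positive direction and can mask or reverse a negative relation. The size is uncertain: r of about +0.06 to +0.41 against sessions, and false significance in about 5% to 99% of studies, under assumed flare risks of 5% to 20% and narrow to wide adherence. It is smaller for the 14-day count and for TUT. The per-session proportion largely removes the bias.

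A lesser, separate point is that the 14-day flare window runs a week beyond the ActivPAL recording, so some flares come after the activity they are meant to explain.

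Neither point touches the primary analysis, the secondary analyses or the sample size.

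**What to change.** 1. Replace the flare count in the compliance models by the proportion of recorded sessions with a flare (rise of at least 20 mm), counting only sessions with both ratings in the denominator.
2. Relate the proportion in days 1–14 to dose in days 15–49, so that predictor and outcome share no sessions.
3. Do not use the whole-period count as a predictor of dose. It can stay as a descriptive summary, next to the number of sessions it is based on.
4. In the physical-activity models, restrict flares to the ActivPAL week and describe the result as a concurrent association only. This does not establish which came first.

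No new data are needed; one derived variable and its time window change. The cost is precision, because the early proportion rests on about 7 sessions or fewer and one session gives only 0% or 100%. Participants without an early session cannot enter the model; their number and later dose should be reported separately.

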HOOS symptoms, pain, QOL	Dose-response relationship	Change in score from baseline to follow up (points, continuous)	Summary statistics for the secondary outcomes will be presented as means with CIs or medians with IQRs within each of the compliance quartiles, and as graphical representation of these values as well.
30-s chair stand test		Change in score from baseline to follow up (repetitions, ordinal/continuous scale)	
Hip muscle strength (isometric)		Change in score from baseline to follow up (Nm/kg), continuous scale)	
3. Exploratory analyses			
Exercise compliance	Exploratory investigation of association. No hypothesis	Time under tension summary dose/week and total (continuous) Number of exercise sessions/ week and total (number, continuous)	Uni-variable regression models. Independent variables will be: pain flares (in the first two weeks of intervention and in the entire intervention period), HOOS pain (baseline), motivation to perform exercises, belief in effect of exercises, self-belief in compliance to exercising, satisfaction with rehabilitation exercise, physical activity (mean upright time/day and mean number of steps/day) and self-efficacy (baseline)
Physical activity level	Exploratory investigation of association. No hypothesis	Mean upright time per day (hours, continuous) and steps per day (numbers, continuous)	Uni-variable regression models. Independent variables will be: pain flares (first two weeks of intervention), HOOS pain (baseline), motivation to perform exercises, self-belief in compliance to exercising, and self-efficacy (baseline).
Result of the operation	Descriptive statistics, no hypothesis	Patient reported rating of perceived result after surgery (ordinal scale)	Data will be presented for each HOOS subscale (pain, symptoms, ADL, QOL) and gait speed. Data will be presented both for each response category, and for the subgroup of patients, who answered "excellent", "very good" or "good" data. This subgroup is considered to be reporting a hip-specific acceptable symptom state. Data will be presented by mean score with 95 % confidence intervals (CI) or median and inter quartile range (IQR). Furthermore, for each exercise dose quartile, the percentage of patients in each response category, will be presented (graphically). Finally, HOOS cut points for PASS will be estimated by the mean score or mean change approach

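### Exploratory compliance models: the raw pain-flare count is coupled to the number of sessions it is meant to explain

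*Protocol article*

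**What the plan says.** Under Other pre-specified outcomes, the visual analogue scale ("VAS) will be used to assess pain before and after each exercise session") is the only source of flares, and "Pain flare is defined as an increase in pain of ≥20 mm". The same entry sets two windows: "Data will be summarized, both for the first 14 days of the intervention and for the entire intervention period". Table 3 (Pain after exercise sessions) gives the scale as a count: "Pain flare for the entire intervention (number, continuous". The first-14-day flare has the same scale.

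In the Exploratory analyses section the compliance models have as "dependent variables: time under tension summary dose and total number of exercise sessions". The predictors begin "Independent variables will be: pain flares (first two weeks of intervention), pain flares (entire intervention period), HOOS pain (baseline". Table 3 (Exercise compliance) confirms the model form: "Uni-variable regression models. Independent variables will be: pain flares (in the first two weeks of intervention and in the entire intervention period". No share, rate, offset or adjustment for the number of sessions is stated. The row is labelled as exploratory, concerned with association, and without a hypothesis.

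**The concern.** Predictor and outcome are built from the same events. A participant who does 25 sessions has 25 chances to record a flare; one who stops after two has two. If flares have no influence on behaviour, the count still rises with sessions. If flares deter exercise, those who are deterred stop generating flares, so the count hides the effect or turns its sign.

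The first-two-week count is affected in two ways. Sessions in days 1–14 are part of the 7-week total, and participants who exercise more early tend to exercise more later.

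The stated aim is to learn what relates to how patients comply, and the Discussion expects the results to help optimise practice and plan a randomised trial. An association created by counting serves neither purpose.

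**Working it through.** The article states no figure for this analysis, so there is none to reproduce. The check is how much correlation the definitions create when flares have no effect.

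**Inputs from the article.** There are 88 participants. Exercise is prescribed every second day for 7 weeks: 49/2 ≈ 25 sessions, of which 14/2 = 7 fall in days 1–14 and 18 later.

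**Assumptions not in the article.** Adherence a varies between patients (beta distribution, mean 0.7, SD 0.2 to 0.3). Flare risk per session has mean μ = 0.05 to 0.20 and between-patient SD τ, and is independent of a.

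**Formulae.** Let S be total sessions and F total flares, with F given S binomial.
- E(S) = 25 × mean(a)
- Var(S) = 25·E[a(1−a)] + 625·Var(a)
- Cov(F,S) = μ·Var(S), which is positive whenever adherence varies
- Var(F) = E(S)(μ − μ² − τ²) + μ²Var(S) + τ²E(S²)
- r = μ·√(Var(S)/Var(F))

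**Whole-period count against total sessions, no true effect.** E(S) = 17.5. With adherence SD 0.2, Var(S) = 25 × 0.17 + 625 × 0.04 = 29.25. With SD 0.3, Var(S) = 25 × 0.12 + 625 × 0.09 = 59.25.

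| Adherence SD | μ | τ | Var(F) | r |
|---|---|---|---|---|
| 0.2 | 0.05 | 0 | 0.904 | +0.28 |
| 0.3 | 0.20 | 0 | 5.17 | +0.68 |
| 0.2 | 0.10 | 0 | 1.868 | +0.40 |
| 0.2 | 0.10 | 0.10 | 5.048 | +0.24 |

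The last two rows differ only in whether flare risk varies between patients; allowing it to vary takes r from 0.40 to 0.24.

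**First-14-day count against total sessions.** Let S1 be the sessions in days 1–14. Cov(S1,S) = 7·E[a(1−a)] + 7 × 25 × Var(a), which is 8.19 at SD 0.2 and 16.59 at SD 0.3. With common flare risk, r = 0.05 × 8.19/√(29.25 × 0.2406) = +0.15 at the low end (μ = 0.05), and 0.20 × 16.59/√(59.25 × 0.994) = +0.43 at the high end (μ = 0.20).

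**Simulation, no true effect, n = 88.**
- Same flare risk for everyone: whole-period r = +0.27 to +0.68, significantly positive in 79–100% of trials; early count +0.15 to +0.43, in 28–100%.
- Flare risk varying between patients (SD 0.10 to 0.20): whole-period r = +0.11 to +0.52, in 11–100%; early +0.10 to +0.38, in 11–99%.
- Separate set-up, adherence mean 0.7 or 0.8, flare risk mean 0.1 or 0.2 with narrow to wide spread: whole-period r = +0.12 to +0.40, in 14–99%; early +0.10 to +0.28, in 10–78%.
- Time under tension as outcome, with an assumed log-SD of 0.4 per session: whole-period r = +0.06 to +0.48; early +0.06 to +0.31.

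**With a true deterrent effect.** In the separate set-up a flare lowers the log-odds of doing the next session. At a drop of 0.5 the mean whole-period correlation is still positive in all 8 scenarios (+0.05 to +0.38). At 1.0 it is positive in 7 of 8 (−0.02 to +0.36).

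**With the share in place of the count (same set-up).** No effect: mean r about 0.00 to 0.01. Deterrence: −0.05 to −0.09 at 0.5 and −0.12 to −0.20 at 1.0. The share in days 1–14 against later sessions gives about 0 under no effect and −0.01 to −0.16 under deterrence. Moving only the outcome window is not enough: with adherence mean 0.8, the early count against later sessions still gives r = +0.07 to +0.13 under no effect.

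**The case against.** **The analysis is exploratory.** Table 3 promises association only, with no hypothesis, and flares are one of many single-predictor models. This stands and limits the severity. It does not remove the point, because the association itself is partly an artefact of counting.

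**The size rests on assumptions.** This also stands. A reader might infer from the common-risk results that the plan will almost always show a significant positive association (79–100% of trials). The article does not support that: it gives no flare distribution, and if risk varies between patients the figure can be as low as 11%. With strong deterrence and very uneven flare risk the coupling can nearly vanish or reverse.

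**The sources differ.** A reader might infer that flares can never exceed recorded sessions. Dose comes from the band sensor, flares from VAS ratings, and the section on missing data warns that sensor data may understate dose. The bound holds for sessions performed, not necessarily for sensor sessions. The direction of the coupling is unchanged.

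**The descriptive outcome.** A reader might infer that the flare count is also faulty as a description. Mean pain change per session and the number of sessions are already planned for reporting, so adding flares per session there is a reporting preference.

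**The remedy has limits.** In simulations of the early share against later sessions with no true effect, ordinary standard errors rejected in 8–15% of trials, HC1 in 7–19% and HC3 in 6–13%. Robust standard errors cannot be claimed to hold the 5% level. Detection is also modest: about 57% in one deterrence setting with adherence SD 0.2, and about 20–25% at SD 0.3.

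**Conclusion.** The point holds for the compliance models. As defined, the flare count tends to correlate positively with compliance when flares have no effect, and it can mask or reverse a deterrent effect. Under the assumed adherence and flare risks, r with total sessions is roughly +0.1 to +0.7 for the whole-period count and +0.1 to +0.4 for the early count. It is smaller where flare risk differs between patients and weaker for time under tension.

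A reader might go further and infer that the plan would conclude that flares do not harm compliance. The article commits to no such conclusion. Severity is minor: the primary and secondary analyses and the sample size of 88 are untouched.

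**What to change.** Change the wording in the Exercise compliance row of Table 3 and in the Exploratory analyses section:

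- Replace the flare count by the share of sessions with paired VAS ratings that were followed by a flare, and name the diary/VAS record as the denominator.
- For early flares, relate the share in days 1–14 to sessions or time under tension in days 15–49.
- Drop the whole-period flare count as a predictor, or label its result as mechanically coupled and non-causal.
- Report the association as an estimate with an interval, for instance weighted by sessions or obtained by bootstrap or permutation, and not as a significance test.

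The inputs are already collected: VAS at each session, and dated sensor records. The cost is that participants with no session in days 1–14 have no share and leave that model. Under the assumed adherence this is 88 × E[(1−a)⁷], about 1 participant at SD 0.2 and 5 to 6 at SD 0.3. They are the least compliant, so their number should be reported.
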